### Data collection

All trial participants will be asked to complete a paper questionnaire at, or just prior to, the baseline clinic appointment and a posted questionnaire after 3, 6 and 12 months postrandomisation (see table 2 for a summary of questionnaire content). Standard Keele CTU procedures will be followed to maximise follow-up, including postcard and questionnaire reminders. In addition, a £10 gift voucher will be sent to participants along with their 3, 6 and 12 months follow-up questionnaires.^60^ At 6 months follow-up, the primary end point, non-responders will be approached for MDC 2 weeks after the reminder questionnaire is mailed. MDC is a shorter version of the self-report outcome questionnaire and will be used to collect the primary and limited secondary outcome measures (KOOS-5), global change scores and EQ-5D-5L, along with date of birth and gender to ensure the data are provided by the intended participant. If no response to the MDC questionnaire, we will attempt to collect minimum data over the telephone by a trial administrator. Data on self-reported adherence to brace use (in the advice, written information and exercise instruction plus knee brace intervention group) will be collected by two-way SMS text messages at 1, 2, 3, 4, 6, 8, 10, 12, 16, 20, 24 and 52 weeks. A schematic diagram of the participant flow chart is provided in figure 1.

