## Objectives

The overall aim of the ‘PROvision of braces for Patients with knee OA’ (PROP OA) trial is to determine the clinical and cost-effectiveness of adding knee bracing (matched to patients’ clinical and radiographic presentation and with adherence support) to advice, written information and exercise instruction compared with advice, written information and exercise instruction alone, in adults with symptomatic knee OA.

Specifically, our primary objective is to determine, in adults with symptomatic knee OA, if the advice, written information and exercise instruction plus knee brace is superior to advice, written information and exercise instruction alone for Knee Osteoarthritis Outcomes Score (KOOS)-5, a composite score of patient-reported pain, other symptoms, activities of daily living (ADLs), function in sport and recreation and knee-related quality of life, at 6 months.

Key secondary objectives are to determine, in adults with symptomatic knee OA:

If the advice, written information and exercise instruction plus knee brace is superior to advice, written information and exercise instruction alone for KOOS-5 at 3 and 12 months.If the advice, written information and exercise instruction plus knee brace is superior to advice, written information and exercise instruction alone for the separate components of KOOS-5 (patient-reported pain, other symptoms, ADLs, function in sport and recreation and knee-related quality of life) at 3, 6 and 12 months.Cost-effectiveness of the advice, written information and exercise instruction plus knee brace compared with advice, written information and exercise instruction alone.

Other secondary objectives are to determine:

If the advice, written information and exercise instruction plus knee brace is superior to advice, written information and exercise instruction alone for: self-reported pain; instability (buckling); treatment response; physical activity; social participation; arthritis self-efficacy.Safety of knee bracing in adults with symptomatic knee OA ((serious)- related adverse events (SAE)).Acceptability and experiences of the trial procedures and interventions to participants receiving and physiotherapists delivering, the trial interventions.Adherence to interventions, including exploring barriers and enablers of adherence to brace use in participants allocated to the advice, written information and exercise instruction plus knee brace intervention.

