**Assessment****						
Demographics	X					
Medical history and physical assessment	X					
Pain manikin	X					
Frequent knee symptoms in last month	X					
KOOS-5*	X			X	X	X
KOOS Activities of Daily Living†	X			X	X	X
KOOS Pain†	X			X	X	X
KOOS Symptoms†	X			X	X	X
KOOS Sports/Recreation†	X			X	X	X
KOOS Quality of Life†	X			X	X	X
KOOS-4	X			X	X	X
Knee pain on weight-bearing activity (0–100 NRS)†	X			X	X	X
Intermittent and Constant Pain (ICOAP)	X			X	X	X
Knee buckling‡	X			X	X	X
Physical activity (IPAQ-E)	X			X	X	X
Arthritis self-efficacy	X			X	X	X
HADS: Anxiety	X					
HADS: Depression	X					
PROMIS Social participation	X			X	X	X
Adverse events			X	X	X	X
Adherence§			X	X	X	X
Patient global rating of change¶				X	X	X
OARSI-OMERACT responder criteria				X	X	X
Treatment acceptability				X		
EuroQol EQ-5D-5L	X				X	X
Healthcare resource use (NHS/private)	X			X	X	X
Out-of-pocket expenses	X				X	X
Time off work	X				X	X

*Primary outcome.

†Key secondary outcomes.

‡Single item used for stratified randomisation, multiple items used for outcome evaluation.

§Obtained in part through: two-way SMS text messages at weeks 1, 2, 3, 4, 6, 8, 10, 12, 16, 20, 24, 52; self-report via questionnaire at 3, 6 and 12 months.

¶Measure used only to classify OMERACT-OARSI responder.

**Close-out at 12 months for analysis of clinical effectiveness.

HADS, Hospital Anxiety and Depression Scale; ICOAP, Intermittent & Constant Osteoarthritis Pain; IPAQ-E, International Physical Activity Questionnaire-Elderly; KOOS, Knee Osteoarthritis Outcomes Score; NHS, National Health Service; NRS, Numerical Rating Scale; OARSI-OMERACT, Osteoarthritis Research Society International; PROMIS, Patient-Reported Outcomes Measurement Information System.

The primary outcome is patient-reported composite knee score of patient reported pain, other symptoms, ADLs, function in sport and recreation and knee-related quality of life (KOOS-5).^49^

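### The 6-month minimum data form omits the weight-bearing pain NRS, the only Table 2 key secondary outcome that KOOS items cannot supply, so this outcome will be more heavily imputed than the primary

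*Protocol article*

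**What the plan says.** Under Data collection, the protocol article states that at 6 months "non-responders will be approached for MDC 2 weeks after the reminder questionnaire is mailed", with a telephone attempt if that form is not returned either. It explains that "MDC is a shorter version of the self-report outcome questionnaire" and that it "will be used to collect the primary and limited secondary outcome measures (KOOS-5), global change scores and EQ-5D-5L". Date of birth and gender are added as identity checks. MDC is described for the 6-month time point only.

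Table 2 schedules "Knee pain on weight-bearing activity" as a 0–100 NRS at baseline and at 3, 6 and 12 months. It gives this measure the same dagger as the five KOOS subscales; the footnote reads "Key secondary outcomes".

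The Objectives rank outcomes differently. Their key secondary list is KOOS-5 at 3 and 12 months, the KOOS-5 components, and cost-effectiveness. Among the other secondary objectives they place "self-reported pain; instability (buckling); treatment response; physical activity; social participation; arthritis self-efficacy".

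Statistical methods says that every model will be reported with missing data imputed, and adds longitudinal mixed-effects models as a consistency check.

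**The concern.** A minimum data form normally follows the outcome hierarchy: the primary outcome first, then whatever ranks next. On Table 2's ranking this form does not. It keeps global change, which has no dagger and which a Table 2 footnote says serves solely for the responder classification. It leaves out an outcome that does have the dagger.

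The omitted outcome is also the one closest to the symptom under treatment. Pain on weight bearing is an inclusion criterion, and participants are advised to use the brace during painful weight-bearing activity. MDC reaches only people who have not answered the questionnaire or its reminder. The observed 6-month NRS values will therefore be fewer than the observed KOOS-5 values and will come only from those who returned the full questionnaire. The gap falls at the primary time point, in a trial whose participants know their allocation.

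**Working it through.** **1. Which daggered outcomes can MDC recover?**

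| Table 2 key secondary outcome | Source | Recoverable through MDC? |
|---|---|---|
| KOOS Pain, Symptoms, ADL, Sports/Recreation, Quality of Life | KOOS items, needed for KOOS-5 | Yes, all five |
| Weight-bearing pain, 0–100 NRS | Separate item | No, not listed |

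**2. The plan's own sample size.** Inputs, from the sample-size paragraph after Figure 1: effect size 0.35, two-sided 5%, 90% power, 20% loss at 6 months.

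- Normal approximation: n per arm = 2 × (1.960 + 1.282)² / 0.35² = 171.6, so 172. The t-based calculation gives 172.5, so 173 per arm, or 346 in total.
- Loss: 346 / (1 − 0.20) = 432.5, so 433, or 434 as an even total.
- Power with 173 per arm at effect size 0.35 is 0.902.

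The stated 346 and 434 reproduce. No stated figure is in dispute.

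**3. Observed 6-month NRS values.** Let m be the share of the 346 expected KOOS-5 responses that arrive only through MDC. The article does not give m, so 5–25% is an assumed range.

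- KOOS-5 observed but NRS missing = 346 × m
- NRS observed = 346 × (1 − m)
- NRS missing, as a share of those randomised = 1 − 346 × (1 − m) / 434
- Complete-case standard error relative to full MDC coverage = 1 / √(1 − m)

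| m (assumed) | KOOS-5 but no NRS | NRS observed | NRS missing | SE ratio | Complete-case power at effect size 0.35 |
|---|---|---|---|---|---|
| 0% | 0 | 346 | 20% | 1.00 | 0.902 |
| 5% | 17 | 329 | 24% | 1.03 | 0.887 |
| 10% | 35 | 311 | 28% | 1.05 | 0.870 |
| 15% | 52 | 294 | 32% | 1.08 | 0.851 |
| 20% | 69 | 277 | 36% | 1.12 | 0.829 |
| 25% | 87 | 260 | 40% | 1.15 | 0.805 |

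Example for m = 10%: 346 × 0.90 = 311; 1 − 311/434 = 0.28; 1/√0.90 = 1.054.

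The power column borrows the effect size planned for KOOS-5; the article makes no power claim for the NRS. Both the SE and the power columns are unadjusted complete-case figures. The planned analysis adjusts for covariates and imputes, so these columns show the loss before imputation recovers any of it.

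**4. What imputation can draw on.** MDC respondents supply KOOS Pain, the rest of KOOS, global change and EQ-5D-5L at 6 months. Many will also have the NRS at baseline and 3 months. Part of the loss is recoverable. How much cannot be computed, because the article gives no correlations.

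**The case against.** The strongest reply has four parts.

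- *The form is short on purpose.* Protecting the primary outcome among reluctant responders is a legitimate trade-off, and ICOAP, buckling, physical activity, self-efficacy and social participation are not listed either. This stands as a reason to keep the form brief. It weighs little against one numeric item on a form that already carries KOOS, global change and EQ-5D-5L.
- *The NRS may not be key.* In the Objectives, self-reported pain is an other secondary objective, so its omission could match its rank. This stands in part: saying that the form loses the only key secondary outcome is true of Table 2's list alone. Cost-effectiveness is key in the Objectives, and its resource-use items are not on the MDC list either. The Objectives' ranking does not fully explain the form, however. Treatment response, which global change serves, sits in the same lower tier and is provided for.
- *The analysis imputes.* A reader might infer that the NRS will be analysed on a smaller and more compliant set than KOOS-5. The article does not support that, since all models are reported with missing data imputed. What differs is the proportion of values that are imputed rather than observed. A reader might also infer a biased treatment effect. Nothing in the article shows that MDC-only response would differ by arm or that such respondents have different pain.
- *The article is condensed.* It is an edited version of the full protocol, and the wording about limited secondary measures is awkward. The sentence nevertheless itemises the form down to its identity checks, so it reads as a complete list. If the form itself already contains the NRS, only this sentence needs correcting.

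**Conclusion.** The point holds as a cheap improvement to data collection, not as a flaw in the primary analysis. As written, MDC cannot recover the weight-bearing pain NRS at 6 months, and on Table 2's list this is the only key secondary outcome so affected. Its missingness will exceed that of KOOS-5 by the MDC share. Its estimate will lean more on the imputation, and so on the missing-at-random assumption that standard imputation makes; the article does not state the imputation's assumptions.

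Over the assumed 5–25% MDC share, 17 to 87 participants would have KOOS-5 without the NRS. Overall NRS missingness would be about 24–40% rather than 20%, and the complete-case standard error would rise about 3–15%. The true cost after imputation is smaller by an unknown amount. KOOS-5, its power, the KOOS subscales and the 3- and 12-month time points are not touched.

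**What to change.** 1. Add the single 0–100 weight-bearing pain NRS item to both the postal and the telephone MDC forms. Place it directly after KOOS, so that it cannot reduce completion of the primary outcome. The cost is a few seconds per respondent and a minor form amendment.
2. Reconcile the status of the NRS: either name it among the key secondary objectives or remove its dagger in Table 2. This is a wording change.
3. If the item is not added, state that 6-month NRS missingness is expected to exceed that of KOOS-5. Say that KOOS Pain and global change will inform its imputation, and cover departures from missing-at-random in a sensitivity analysis. This costs no data collection, but it replaces values that could have been observed with assumptions.

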**Figure 1 F1:**
[figure not shown]
Participant flow and timeline. CTU, Clinical Trial Unit; GP, general practitioner; OA, osteoarthritis.

Bracing trials show standardised effect sizes (ES) for short-term improvements in knee pain and function of 0.33–0.56 and 0.22–0.48, respectively, for tibiofemoral unloading braces^24^ and 0.61 and 0.39, respectively, for soft neoprene sleeve braces.^25^ Our trial is powered to detect a between-group ES of 0.35 (small-to-medium effect) in the primary outcome at 6 months with two-sided 5% significance and 90% power, which, assuming an SD of 23 as estimated from previous trial data,^44^ equates to a minimum clinically important difference (MCID) of 8-points on the KOOS-5; an MCID value that aligns with published evidence for the tool.^61^ We will randomise 434 patients, recruited over a period of 24 months, to allow for 20% lost to follow-up at 6 months,^44 46 62^ (target n at 6 months=346; 173/arm). We have not inflated our sample size for therapist effects as each physiotherapist will be trained to deliver both interventions, however, the therapist will be included as a covariate in a sensitivity analysis of the treatment models to increase model power.^63^

### Statistical methods

A separate a priori data analysis plan will be written to describe all trial analysis. Consequently, only a brief outline is outlined below.

A Consolidated Standards of Reporting Trials flow diagram will describe the flow of participants through the study and will include reasons for trial withdrawal if given. Descriptive statistics will be used to describe the key baseline characteristics of participants at each stage of recruitment and follow-up, and by intervention arm. The primary outcome analysis will be on an intention-to-treat basis and will compare the primary outcome (KOOS-5) at the primary endpoint (6 month follow-up) for advice, written information, and exercise instruction plus knee bracing versus advice, written information and exercise instruction alone. Secondary analysis will include the analysis of the primary outcome at 3 and 12 months (ie, the secondary endpoints) and the secondary clinical effectiveness outcomes at 3, 6 and 12 months. Analysis of covariance will be used to model outcomes that are continuous and logistic regression for those that are dichotomous. All models will be reported after adjustment for a priori analysis covariates (as defined in the a priori analysis plan) and after imputation of missing data. Treatment effect estimates will be presented as mean differences or ORs (as appropriate) with 95% CIs. Longitudinal mixed-effects models will also be used to evaluate the treatment effect at each single time point and over time to check that results are consistent with those derived from the primary analysis.

Exploratory subgroup analyses will be performed (if numbers in each subgroup are sufficient for these analyses to be feasible) based on the presence of knee instability (buckling), predominant knee compartment involved, level of adherence and anxiety/depression. Participants will also be included in a per-protocol analysis if they meet prespecified inclusion criteria, defined fully in the a priori analysis plan. Cross-tabulation and the kappa statistic will be used to test how accurate brace allocation would have been if based on clinical judgement alone, rather than on clinical assessment findings and X-ray assessment combined. Treatment acceptability will be described using numbers and percentages. Any adverse events and protocol violations will be reported throughout the trial by intervention arm. No interim analysis will be undertaken during the trial to assess the clinical effectiveness of advice, written information and exercise instruction plus knee bracing over advice, written information and exercise instruction alone, however, an internal pilot trial phase will be conducted with prespecified progression criteria (online supplemental datafile 1).

### Economic evaluation

#### Within trial economic evaluation

An economic evaluation will be undertaken alongside the trial to estimate the cost-effectiveness of advice, written information and exercise instruction plus knee bracing versus advice, written information and exercise instruction alone in the management of knee OA. An incremental cost–utility analysis will estimate cost per quality-adjusted life year (QALY) over 12 months follow-up. QALYs will be calculated from responses to the EQ-5D-5L questionnaire using the ‘area under the curve’ approach. The cross-walk value set to obtain utility scores, in line with current NICE recommendations^64^ and the more recent English value set will be used in a sensitivity analysis. The base-case analysis will be from a healthcare perspective, with an additional analysis from a societal perspective taking into account out-of-pocket costs and work productivity losses. Mean resource use (for each category of healthcare usage) and mean total costs will be calculated for all trial participants. Analysis of productivity losses will use the human capital approach, and the self-reported days of absence will be multiplied by the respondent-specific wage rate. Multiple imputation will be used to impute all missing values for the EQ-5D and total cost estimates for missing data at follow-up. Incremental cost–utility analysis will be undertaken to estimate the incremental cost per QALY gained, adjusting for baseline covariates. The robustness of the results will be explored using sensitivity analysis. Cost-effectiveness acceptability curves will also be produced to reflect the probability the intervention will be cost-effective at different cost per QALY willingness to pay thresholds.

#### Model-based health economic analysis

Decision modelling, using a Markov model, will also be undertaken to extend beyond 12 months follow-up, to extrapolate costs and QALYs over a lifetime time horizon. The cost–utility analysis will be from an NHS perspective, with discounting of costs and outcomes at 3.5%. In addition to trial data, the model will be populated with data from existing literature on the natural history of symptomatic knee OA, risks associated with surgery and quality of life, and national data on all-cause mortality. The model will be subject to deterministic sensitivity analysis by changing individual parameter values and changing model assumptions, and probabilistic sensitivity analysis to simultaneously incorporate all parameter uncertainty. Cost-effectiveness planes and cost-effectiveness acceptability curves will be presented to show the probability that advice, written information and exercise instruction plus knee bracing is cost-effective at different cost/QALY thresholds.

### Nested qualitative studies

In addition to qualitative interviews undertaken in the internal pilot phase (online supplemental datafile 1), a theoretically informed qualitative study will be completed within the main trial, which builds on our previous work exploring acceptability of, and adherence to, physiotherapy-led interventions for individuals with knee OA, and barriers and facilitators to non-pharmacological interventions (exercise and physical activity) in this population.^65–67^

To help explain the results of the trial in terms of the comparable clinical effectiveness of interventions, a qualitative study will investigate contextual factors, and barriers and enablers to brace use in individuals with knee OA. Drawing on normalisation process theory (NPT)^68 69^ and the theoretical domains framework (TDF),^70^ we will investigate patient and physiotherapy perspectives and will undertake:

Semistructured interviews (face to face or telephone) with ≤40 participants postintervention (at 6 months follow-up) (n≤20 from each treatment arm). Participants will be purposefully sampled from both treatment arms (using data from trial questionnaires and SMS text messages) to ensure a diverse range of characteristics including age, sex, knee compartmental involvement, baseline pain severity, presence/absence of buckling, perceived overall improvement and level of adherence. The interview topic guide will explore participants’ experiences of trial interventions, adherence to interventions (including barriers and enablers to brace adherence in the advice, written information and exercise instruction plus knee brace intervention arm), and impact of interventions on participants’ symptoms, functioning and quality of life. Perceived harms and adverse events from interventions will also be explored. Data collection and analysis will be carried out iteratively so that emerging themes can be effectively explored in subsequent interviews.^71^ Sampling will continue until no new themes emerge.

Semistructured interviews will be conducted with physiotherapists who delivered trial interventions (n≤16) after they have treated their final trial participant. Interviews will provide insight into experiences of implementing, embedding, accepting and integrating both advice, written information and exercise instruction and the addition of knee bracing into NHS physiotherapy services. The topic guide will cover the appropriateness of the trial training programme, physiotherapists’ views of their roles in the trial in terms of delivering usual practice (advice/education/exercise prescription) but in only one treatment session, and in the advice, written information and exercise instruction plus knee bracing arm, the extra activity including using a standardised clinical assessment to identify compartment of knee affected by OA, assessment of X-rays, prescribing a brace and supporting the patient to use it, changing it where necessary, and using brief MI techniques specifically to facilitate adherence to brace use.

All interviews will be audiorecorded, transcribed verbatim, checked and anonymised for analyses. Initially, each interview transcript will be read and reread to identify and code discrete parts of the data that represent a particular concept. As analysis continues, using principles of constant comparison,^71^ data will be closely examined for similarities and differences, and groups of words or phrases representing the same concept will be grouped into themes. Emerging codes and themes will be discussed and agreed with members of the study team (including PPIE team members) on an ongoing basis and applied to the dataset with ongoing refinement as needed. Inductive analysis (described above) will precede deductive analysis and mapping of themes to TDF or NPT constructs.^68 70^ This layered approach enables a rich interpretative analysis to be completed as emergent issues are identified ahead of making sense of data according to theoretical constructs.^68 72^ Data will be used to inform an implementation strategy in conjunction with Keele’s Impact Accelerator Unit.

